## Research Design and Methods

Describe the research design and methods and procedures to be used in achieving the specific aims of the research project. If applicable, mention the type of personal protective equipment (PPE), use of aerosol confinement, and the need for the use BSL2 or BSL3 laboratory for different part of the intended research in the methods.. Define the study population with inclusion and exclusion criteria, the sampling design, list the important outcome and exposure variables, describe the data collection methods/tools, and include any follow-up plans if applicable. Justify the scientific validity of the methodological approach (biomedical, social, gender, or environmental).

Also, discuss the limitations and difficulties of the proposed procedures and sufficiently justify the use of them.

**Study design:** Open label, randomized, controlled intervention study in 308 children between two months to 59 months admitted to the Dhaka Hospital of icddr,b . Children will be randomized to receive (i) Amoxicillin plus single dose Gentamicin (ii) four doses of parenteral Ampicillin plus single dose Gentamicin. After 72 hours of treatment injectable Amoxicillin or injection Ampicillin will be switched to or replaced by oral Amoxicillin.

## Eligibility Criteria

Selection of the study population is based on the fact that there should be a sufficient proportion of patient who has true bacterial pneumonia or sepsis. If the study enrolls a large proportion of children with bronchiolitis, or viral pneumonia then those with true severe pneumonia will be diluted and the power to see a difference is reduced. Therefore, to yield actual response to therapy we strengthen the entry criteria of enrolment.

### *Inclusion criteria:*

Children more than 2 months to less than 59 months will be enrolled in our study, if they have a history of cough or difficulty in breathing and WHO classified severe pneumonia plus **at least two of the following:**

- i) Central cyanosis or oxygen saturation <90% on pulse oxymetry
- ii) Severe respiratory distress (e.g. grunting, very severe chest indrawing)
- iii) Signs of pneumonia with a general danger sign: inability to breastfeed or drink; lethargy or reduced level of consciousness; convulsion
- iv) In addition, some or all of the other signs of pneumonia may be present, such as:
  - Signs of pneumonia [age specific fast breathing( *Annex I*)]
  - Chest indrawing: lower chest wall indrawing
  - Chest auscultation signs: (any one)
    - a) Decreased breath sounds
    - b) Bronchial breath sounds
    - c) Crackles
    - d) Abnormal vocal resonance (decreased over a pleural effusion or empyema, increased over lobar consolidation)
    - e) Pleural rub

### *Exclusion Criteria:*

Children with life threatening condition that required immediate assisted ventilation or refer to outside hospital (such as septic shock, cardiac arrest, apnea, respiratory failure etc.) will be excluded from the study. Children with uncorrected cyanotic CHD, hypercapnoea ( $\text{PCO}_2 > 60\text{mm of Hg}$ ), status asthmaticus and upper-airway obstruction, preterm baby (but not ex-preterm) and those for who informed consent can't be secured from their parents/ care-givers. Care giver presented with any drug container of antibiotics or prescription showing getting antibiotics will be excluded.

### **Study site and procedure:**

This study will be conducted at the Dhaka Hospital of icddr, Dhaka, Bangladesh. This hospital is located in Dhaka city, the capital of Bangladesh. It provides care and treatment to around 110,000 diarrheal patients with or without associated complications and with or without other health problems each year. The vast majority of the patients come from poor socio-economic backgrounds from urban and peri-urban Dhaka, the capital city of Bangladesh.

Patients attending this hospital are first assessed by an experienced triage nurse, which include assessment of the type of diarrhoea and degree of dehydration, and presence of other health problems including ALRI/ pneumonia, severe malnutrition, impaired mental status (convulsion), and sepsis. They redirect non-diarrhoeal patients to other appropriate city hospitals in the city. Based on assessment of diarrhoeal patients, those with uncomplicated illness without signs of dehydration are referred to the Out Patient Unit for 4-5 hours of observation, maintenance of hydration using ORS solution, and for provision of health education to the mothers/caregivers. Those with some and severe dehydration but without any associated health problems are admitted to Short Stay Ward (SSW) for correction of dehydration and maintenance of hydration using ORS and/or intravenous fluids, provision of antimicrobial therapy as appropriate, with an average stay of 24 hours. Those with associated complications of diarrhoea and/or associated health problems are referred to a physician for assessing the need for admission to either the Longer Stay Ward (LSW) or Acute Respiratory Ward (ARI) or to the Intensive Care Ward (ICU) depending on the clinical severity. The usual associated conditions include difficult respiration, cyanosis, apnoea, hypothermia or hyperthermia, marked lethargy or comatose condition, poor peripheral perfusion not attributable to severe dehydration. Those hospitalised in SSW are assessed by hospital clinicians for possible admission to LSW and further workup and management. After admission to the LSW/ARI/ICU the attending physician obtained medical history, performs thorough clinical examination, makes a problem list including differential diagnoses for each of them, arranges for required laboratory workups, and develops the treatment plan following standard guidelines of the hospital. They also perform bedside procedures such as sampling blood, performing lumbar puncture etc. Oxygen saturation is determined by pulse oxymeter when necessary, and blood glucose estimated by bedside Gluco Check machine in nearly all patients admitted to the LSW/ARI/ICU.

### **Study Interventions:**

Children between 2 months to 59 months with severe pneumonia will be studied to evaluate the proportions of treatment failure in two different arms.

We will use sealed envelopes to randomly assign the children to either treatment arms. In first arm children will receive 2 daily doses of parenteral Amoxicillin and single daily dose of parenteral Gentamicin; and in 2nd arm, children will receive 4 daily doses of parenteral Ampicillin and single daily dose of parenteral Gentamicin. After 72 hours of treatment, injection Amoxicillin and injection Ampicillin will be replaced with oral Amoxicillin but injection gentamicin will be continued for total 5 days in once daily dose. During this time patient will be suggested to discharge from hospital and attend to Ambulatory care unit for getting once daily dose of injection Gentamicin. Both the treatment arm will continue for 5 days.

During the study period, children in both study arms will also receive standardized hospital management for diarrhoea and malnutrition (*Annex 2,3*).

“Treatment failure” will be standardized, based on clinical and monitoring data. Treatment failure is defined by the persistence of danger signs of severe pneumonia for >48 hours or deterioration within 24 hours of initiation of therapy or if child needs mechanical ventilation, dies at any time during hospital stay or left the hospital against medical advice.

During the study period any child from either study group who develops the features of “clinical failure” (any two of three criteria in the definition below) will be managed according to best practice in the clinical context. If children fail any arm of treatment, they should be rescued with second line antibiotic regimen, which is injection ceftriaxone and injection levofloxacin. Hypoxia will be managed by B-CPAP or humidified high flow air / O2 mix at 2 l/kg/min through nasal cannula.

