## Project Summary

[The summary, within a word limit of 300, should be stand alone and be fully understandable.]

Principal Investigator: [name]

Research Protocol Title: Efficacy of two doses of parenteral Amoxicillin plus single dose Gentamicin compared to four doses of parenteral Ampicillin plus single dose Gentamicin in managing children hospitalized with WHO classified severe pneumonia: an open labelled randomized controlled clinical trial

Proposed start date: 15 September 2017

Estimated end date: 14 September 2018

Background (brief):

**Burden:** Pneumonia remains the leading infectious cause of death accounting 920,000 children under five around the world. This means a loss over 2,500 child lives every day, or over 100 every hour. Since 2000, the number of child deaths caused by pneumonia has decreased by 47 per cent. The tremendous progress made is due in part to the rapid roll-out of vaccines, better nutrition and improved care-seeking and treatment for symptoms. However, pneumonia hasn't declined as quickly as other diseases such as malaria (58%), HIV/AIDS (61%) and measles (85%).

**Knowledge gap:** The Lancet Series on Childhood Pneumonia and Diarrhea has reported that case management is one of the three most effective interventions to reduce pneumonia deaths in children. It is also noted that cost effectiveness of these interventions in national health system needs urgent assessment. It was suggested to find out means to reduce hospital stay without compromising the quality of care.

**Relevance:** The main purpose of our study is to compare the efficacy of two doses of parenteral Amoxicillin plus single dose Gentamicin compared to four doses of parenteral Ampicillin plus single dose Gentamicin. After 72 hours of treatment injectable Amoxicillin or injection Ampicillin will be switched to or replaced by oral Amoxicillin and will be discharged with an advice to attend to Ambulatory Care Unit (ACU) to receive once daily dose of injection Gentamicin for total 5 days. It is anticipated that this modified therapy will reduce hospitalization stay of children with severe pneumonia and would therefore be relevance in countries with resource poor setting. By reducing hospitalization period, this therapy has potentials to reduced hospital acquired infection.

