#### Secondary objectives:

To compare time to resolution of danger signs of pneumonia, length of hospital stay, mortality rate, rate of complication requiring mechanical ventilation, and rate of multiorgan or renal or cardiac failure between the two treatment groups.

**Methods:** This will be an open labelled randomised, controlled trial in (n= 308) of children of 2-59 months of age hospitalized with WHO classified severe pneumonia. Eligible children will be randomized to one of two treatment regimens: (i) two daily doses of parenteral Amoxicillin plus single daily dose of Gentamicin  
(ii) four daily doses of parenteral Ampicillin plus single daily dose of Gentamicin.

After 72 hours of treatment with parenteral amoxicillin or parenteral ampicillin, injectable form will be replaced by oral amoxicillin. We will be evaluating the response to therapy in both the arms.

The response of treatment will be measured by clinical improvement in terms of normalization of fast breathing, chest indrawing, fever and improvement of general condition, feeding, and well being. In other terms end point of the study will be treatment failure, which is defined as follow.

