**Treatment failure:**

Treatment failure is defined by the persistence of danger signs of severe pneumonia for >48 hours or deterioration within 24 hours of initiation of therapy or if child needs mechanical ventilation, dies at any time during hospital stay or left the hospital against medical advice.

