**Danger Sign:**

- i) Inability to breastfeed or drink
- ii) Lethargy or reduced level of consciousness
- iii) Convulsions

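### The 72-hour switch to oral amoxicillin depends on time alone, so a child still hypoxaemic and in severe respiratory distress can be stepped down under the stated rule

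*Protocol*

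**What the plan says.** The protocol gives the switch rule four times:

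- Study Interventions: "After 72 hours of treatment, injection Amoxicillin and injection Ampicillin will be replaced with oral Amoxicillin".
- Project Summary, Relevance paragraph: "After 72 hours of treatment injectable Amoxicillin or injection Ampicillin will be switched to or replaced by oral Amoxicillin and will be discharged".
- Project Summary, Methods paragraph: "After 72 hours of treatment with parenteral amoxicillin or parenteral ampicillin, injectable form will be replaced by oral amoxicillin".
- Research Design and Methods, Study design: "After 72 hours of treatment injectable Amoxicillin or injection Ampicillin will be switched to or replaced by oral Amoxicillin".

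None of these asks for improvement, a saturation level, resolved distress or ability to swallow. Study Interventions keeps injected gentamicin going once daily to day 5, so only the beta-lactam changes route.

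Clinical conditions are written for other decisions. Discharge criteria require, among other things, resolved distress, saturation above 90% and good feeding. Ambulatory care Unit limits that service to children who have recovered and are improving. Signs of Improvement says what should be seen within 2 days, but names no action if it is not seen. Study Interventions reserves the second-line regimen (ceftriaxone plus levofloxacin) for children who fail an arm.

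**The concern.** A switch from injected to oral antibiotic in a very ill child is normally tied to how the child is doing. Here it is tied to elapsed time. The protocol's own exits from first-line treatment depend on treatment failure, and the persistence limb of that definition looks only at general danger signs. Hypoxaemia and severe respiratory distress are entry criteria of equal rank, yet their persistence triggers nothing in the antibiotic plan.

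What is at stake is the care of a child who at 72 hours still satisfies two of the criteria that made the pneumonia severe. Followed literally, the rule withdraws the injected beta-lactam from that child. A physician who prefers to continue it has to rely on general wording elsewhere in the protocol.

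**Working it through.** The point rests on text and not on a stated figure; the sample size of 154 per group is not involved. The check is whether an eligible child can reach 72 hours with unresolved severe illness and no protocol event.

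**1. Entry without a danger sign.** Inclusion criteria ask for at least two items from a list. Item i is "Central cyanosis or oxygen saturation <90% on pulse oxymetry"; item ii is severe respiratory distress; item iii is pneumonia with a general danger sign; item iv covers other signs. A child with i and ii qualifies. Counting combinations of two or more items:

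- If only i to iii count: 3 pairs + 1 triple = 4 combinations. One lacks a danger sign, and it is i + ii.
- If item iv also counts: 6 pairs + 4 triples + 1 quadruple = 11. Four lack item iii (i+ii, i+iv, ii+iv, i+ii+iv). Two of these contain both hypoxaemia and severe distress (i+ii and i+ii+iv).

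These are routes into the trial, not numbers of children. They show that the route exists and say nothing about how often it is used.

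**2. What counts as a danger sign.** The Danger Sign list has three entries: inability to feed or drink, "Lethargy or reduced level of consciousness", and convulsions. Low saturation and respiratory distress are not on it. Annex 1 keeps them apart in the same way.

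**3. The failure definition at 72 hours, limb by limb,** for a child with persisting i and ii and no danger sign:

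| Limb | Source | Met? |
|---|---|---|
| Persistence or early deterioration: "the persistence of danger signs of severe pneumonia for >48 hours or deterioration within 24 hours of initiation of therapy" | Treatment failure; Study Interventions | No: there is no danger sign to persist, and an unchanged state is not deterioration |
| Clinical respiratory failure | Specific Aims, Primary Outcome | No: listed only as an example of deterioration in the first 24 h |
| Mechanical ventilation, death in hospital, leaving against advice | Treatment failure; Study Interventions | No, by assumption |

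No limb is met, so the second-line rule does not apply. The hypoxia sentence in Study Interventions concerns respiratory support and gives no antibiotic instruction.

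**4. Timing.** Signs of Improvement expects a response by 48 h and the switch falls at 72 h: 72 − 48 = 24 h. With physician review at least every 12 h (Monitoring section), that is 24 / 12 = 2 reviews at which non-response could be noticed, with no link to the switch.

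**5. Room to hold the child back.** The course lasts 5 days = 120 h, and 120 − 72 = 48 h. That is 48 / 12 = 4 scheduled reviews (84, 96, 108 and 120 h). Extra doses at most: 2 days × 4 = 8 of ampicillin, or 2 days × 2 = 4 of amoxicillin.

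**The case against.** The strongest reply is that the protocol does not force the step-down. Discharge criteria accept a finished parenteral course as an alternative to tolerating oral drugs, so a child who stays on injections is foreseen. Laboratory investigations defers to the hospital's pneumonia guideline, and Respiratory ward Infrastructure bases therapy on clinical evaluation. Study Interventions sends clinical failure to best practice; its three criteria are not given, so this child may or may not be covered.

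This stands against a stronger reading. A reader might infer that stepping down is the only antibiotic instruction this child has, or that a physician who continues injections plainly breaches the protocol. The document does not support either. But none of these texts puts a condition on the switch, and the four statements of the rule are specific and agree with each other.

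Other replies:

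- *Harm is not shown.* Correct. The background cites 3 to 5 days of parenteral treatment, and 72 h lies within it, so no departure from that guideline can be inferred. The Pharmacokinetics section calls oral and intramuscular amoxicillin similar. It also puts the intravenous bolus peak at 6 to 12 times the intramuscular one, and it does not address a child who is still hypoxaemic.
- *A sick child would be sent home.* The Project Summary wording might suggest this, but Discharge criteria and Ambulatory care Unit govern discharge. The gap concerns the oral switch only.
- *Respiratory status is already recorded.* It is: CRF items 112 to 135 capture severe hypoxaemia (below 85%), severe indrawing and grunting on days 1 to 3. Recording does not supply an action.
- *A conditional switch brings unblinded judgement into an open-label non-inferiority trial.* This has force against any discretionary move to second-line drugs that leaves the failure definition unchanged, because rescued children would then count as non-failures. It has much less force against holding the assigned injections on criteria fixed in advance.

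**Conclusion.** The concern holds in a limited form. The switch rule is time-only in all four places, and an eligible child can have persisting hypoxaemia and severe distress at 72 hours without meeting any failure limb. Under the stated rule that child is stepped down. Other passages permit judgement but do not condition the switch.

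The conclusion assumes that danger signs means the three signs in the protocol's own list, and that the undefined clinical failure clause cannot be relied on to catch this child. The number of children affected is unknown. The rule is identical in both arms, gentamicin continues, and no effect on the primary outcome, on deaths or on the direction of any bias is shown. A reader might infer a threat to the treatment comparison; the document gives no basis for that. This is a patient-safety clarification and a cheap improvement.

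**What to change.** In the four places that state the rule, say that in both arms the switch to oral amoxicillin takes place at 72 hours only if the clinical items of Discharge criteria are met: distress resolved, saturation above 90%, feeding well, able to take oral medication. Otherwise the assigned injections continue within the 5-day course, with reassessment at the existing 12-hourly physician review.

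Keep second-line antibiotics tied to failing an arm, as Study Interventions has it now. Add no discretionary rescue that leaves the failure definition unchanged.

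Bring the discharge wording in the Project Summary into line with Discharge criteria. Add rows for injectable and oral amoxicillin, with date and time of the switch, to CRF item 141, which has neither. No new status fields are needed.

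The cost is a conditional sentence in four places and two CRF rows. For each child held back it is up to 48 hours more injections and stay (8 ampicillin or 4 amoxicillin doses at most). Some of that stay would be needed anyway, since Discharge criteria already keep a child in distress on the ward. The total cannot be stated because the number of such children is unknown. No extra patients are needed.

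The change does not settle what a child receives who never improves and yet meets no failure limb. That remains with the missing definition of clinical failure.

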### **Discharge criteria**

- Respiratory distress has resolved
- Oxygen saturation > 90%
- Feeding well
- Able to take oral medication or have completed a course of parenteral antibiotics
- The parents understand the signs of pneumonia, risk factors and when to return

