### **Ambulatory care Unit:**

This is a new set up in Dhaka Hospital and the facility is used to reduce patient hospital stay as well as nosocomial infection rate. This facility is only offered to the patients who have recovered from the acute illness and showing signs of improvement. The patients who live in Dhaka city and able to return to Dhaka hospital are requested to come to receive injectable drugs every morning. Drugs will be provided from hospital free of cost. The total procedure will take less than one hour and patient can go home afterward. By this care the antibiotic course will be completed and hospitalization cost can be minimized.

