### **Sample size calculation:**

[For two-sample comparison of proportion (non-inferiority)]

Null hypothesis:  $p_2 - p_1 \leq \delta$  (inferior), where:  $p_i$  (entered in command) is the overall proportion of participants expect to experience the outcome if the treatments are non-inferior, and delta is the smallest change in proportions between groups ( $p_2 - p_1$ ) which would still be clinically important.

Assumptions:

power = 0.8; alpha = 0.025 (one-sided);  $p_i = 0.50$ ; delta = 0.16

Estimated required sample size (per group) = 154,

Total sample is 308

**Primary Outcome:** Treatment failure which is defined by the persistence of danger signs of severe pneumonia for >48 hours or deterioration within 24 hours of initiation of therapy (development of new danger signs or clinical signs of respiratory failure, or development of severe sepsis/meningitis, or, radiological deterioration).

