### **Secondary outcomes:**

1. Time to resolution of danger signs of severe pneumonia
2. Length of hospital stay
3. Death during hospitalization

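### Length of hospital stay is an insensitive secondary outcome here, and the shorter stay the protocol anticipates comes from a 72-hour pathway given to both arms

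*Protocol*

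**What the plan says.** The Project Summary describes the oral switch, discharge and ambulatory gentamicin, and then states: "It is anticipated that this modified therapy will reduce hospitalization stay of children with severe pneumonia". It adds that a shorter stay could lower hospital-acquired infection. Length of stay is also a secondary objective, and "Length of hospital stay" is listed as a secondary outcome under Specific Aims, under Sample Size Calculation and under Outcome variables.

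The intervention text applies one pathway to both groups. Study Interventions says: "After 72 hours of treatment, injection Amoxicillin and injection Ampicillin will be replaced with oral Amoxicillin". Gentamicin continues once daily to complete five days, and the text goes on: "During this time patient will be suggested to discharge from hospital and attend to Ambulatory care unit for getting once daily dose of injection Gentamicin". Only the first 72 hours of parenteral treatment differ between arms: amoxicillin twice daily or ampicillin four times daily.

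Three further statements bear on when a child leaves:

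- Discharge criteria lists conditions with no clock, starting with "Respiratory distress has resolved" and including saturation above 90% and feeding well.
- Ambulatory care Unit offers the service only to recovered, improving children, and adds: "The patients who live in Dhaka city and able to return to Dhaka hospital are requested to come to receive injectable drugs every morning".
- The Project Summary words discharge as following directly from the 72-hour switch, whereas Study Interventions only suggests it.

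**The concern.** A reader of the Project Summary would expect the trial to show that the new regimen shortens hospitalisation. But the element that could free a bed early, the switch to oral treatment with gentamicin given as an outpatient, is not randomised. The control group receives it as well, so no arm lacks it and the trial has no contrast from which to estimate its effect.

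For the contrast that is randomised, stay is a blunt measure of recovery. If children are kept until the 72-hour switch, one who is well at 40 hours and one who is well at 65 hours have the same stay. A null result could be reported as equal recovery when it mainly reflects a shared rule. Residence may blur the outcome further, and unreconciled wording on discharge leaves room for staff who know the allocation to fill the gap.

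**Working it through.** **1. The protocol's only computed figure.** Inputs from Sample size calculation: "power = 0.8; alpha = 0.025 (one-sided"), expected proportion 0.50, margin 0.16. The formula is n per group = 2p(1−p)(z₀.₉₇₅ + z₀.₈₀)²/δ². With numbers: 2 × 0.25 × (1.960 + 0.842)²/0.16² = 0.5 × 7.849/0.0256 = 153.3, rounded up to 154. The protocol agrees: "Estimated required sample size (per group) = 154". This figure concerns treatment failure. No effect size, SD or power is given for stay.

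**2. What 154 per arm gives for a continuous outcome.** Detectable standardised difference at 80% power, two-sided 5%: √(2/154) × (1.960 + 0.842) = 0.114 × 2.802 = 0.32.

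**3. Effect of a shared 72-hour floor.** The protocol gives no distribution for recovery time, so every value here is an assumption.

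- Time to clinical readiness is lognormal with log-SD 0.5. The slower arm has median M and the faster arm M − 12 hours.
- Stay = max(readiness, 72 h). For a share q without ambulatory access, stay = max(readiness, 120 h).
- 154 per arm, 1,500 simulated trials, Mann-Whitney test at two-sided 0.05. Cells show mean difference in stay and power.

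| M | No floor | 72 h floor | Floor, q = 20% | Floor, q = 40% |
|---|---|---|---|---|
| 48 h | 13.7 h; 1.00 | 3.8 h; 0.90 | 3.2 h; 0.40 | 2.5 h; 0.17 |
| 72 h | 13.7 h; 0.89 | 8.6 h; 0.80 | 7.4 h; 0.54 | 6.5 h; 0.38 |
| 96 h | 13.7 h; 0.64 | 11.2 h; 0.58 | 10.6 h; 0.51 | 9.3 h; 0.40 |

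With no true difference the rejection rate was between 0.04 and 0.06 in every setting. The floor and the residence-driven stays therefore dilute the contrast without biasing it.

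The first row shows why. With medians of 48 and 36 hours, the shares ready before 72 hours are Φ(ln(72/48)/0.5) = Φ(0.81) = 79% and Φ(ln(72/36)/0.5) = Φ(1.39) = 92%. For most children the 12-hour gain never appears in the stay. The floor alone shrinks the effect more than the power; the larger power losses come when some children stay to 120 hours.

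**4. Residence noise.** If a share q stayed two days longer (120 − 72 = 48 h), the added SD would be 2√(q(1−q)) days: 0.80 at q = 0.2, 0.92 at q = 0.3 and 0.98 at q = 0.4. Both the two days and q are assumptions. The protocol does not say where children outside Dhaka city receive gentamicin on days 4 and 5, or what share they form. Study site and procedure says only that the vast majority of patients come from urban and peri-urban Dhaka.

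**5. Recording.** CRF items 2 to 4 take calendar dates without times, and item 4 combines discharge with transfer to the NRU. That coarsens stay further.

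**The case against.** A reader might infer that stay cannot be compared at all, or that the protocol forces a null result. The documents do not support that. Discharge is suggested rather than mandated, clinical criteria apply, and ambulatory care requires recovery, so stay still responds to recovery that takes longer than 72 hours. Children who fail go to rescue treatment and may stay longer, and the planning proportion of 0.50 implies that the protocol expects failures to be common. In the illustration, with the floor alone, 3.8 to 11.2 hours of contrast remain with power 0.58 to 0.90.

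A reader might also infer that any difference in stay would merely reflect where families live. Residence is a baseline factor, balanced in expectation by randomisation and recorded in CRF item 15. It adds noise and can be adjusted for.

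It can further be said that the anticipated shorter stay is background text, not the stated hypothesis; that actual stay matters for the planned cost analysis; that the discharge passages can be read together, with the switch making discharge possible and the criteria gating it; and that recovery speed is already captured through time to resolution of danger signs and CRF items 147 to 149.

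Most of this stands, and it is why actual stay should be kept. The last two points stand only in part. The discharge criteria can be met before or after 72 hours, and the Project Summary states discharge without any condition. Time to resolution of danger signs is undefined for a child enrolled on hypoxaemia plus severe respiratory distress without a danger sign, which the inclusion criteria allow. Items 147 to 149 cover neither saturation nor feeding.

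**Conclusion.** The point holds in a limited form. The shorter stay anticipated in the Project Summary is tied to a pathway that both arms receive, so this comparison cannot show it. That follows from the text and needs no assumption.

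For amoxicillin versus ampicillin, length of stay is insensitive rather than unanswerable. Recovery differences before 72 hours are largely hidden, and residence-dependent ambulatory access may add noise but not bias. Under the assumed values, a true 12-hour difference in median readiness, worth 13.7 hours in the mean, shows up as 3.8 to 11.2 hours of stay with the floor alone, and as 2.5 to 10.6 hours if 20% to 40% of children stay to 120 hours. The real loss is unknown, because the recovery distribution, the share outside the city and their arrangements for days 4 and 5 are not given. The primary endpoint is not affected.

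**What to change.** 1. **Project Summary.** Attribute the anticipated shorter stay to the 72-hour switch and ambulatory pathway common to both arms, and do not present it as a benefit this comparison can show.
2. **Secondary outcomes and Outcome variables.** Add, beside actual stay, the time from first study dose to the first physician review at which the clinical discharge criteria (distress resolved, saturation above 90%, feeding well) are all met. Read it at the 12-hourly physician reviews already required under Monitoring, with one dated and timed CRF line. Count children who die, are ventilated or leave against advice as not having met the criteria.
3. **Actual length of stay.** Keep it, and analyse it stratified by or adjusted for residence (CRF item 15). State in advance that a null result is uninformative about recovery before 72 hours.
4. **Discharge wording.** Reconcile the Project Summary, Study Interventions and Discharge criteria on what triggers discharge. Which rule should apply is a clinical matter for the investigators.

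Cost: one extra CRF line and some rewording. The added outcome is still judged by unblinded physicians and resolves time only to about 12 hours. The claim about stay becomes weaker.
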